**Figure 1 fig1:**
[figure not shown]
Study flow chart. VR, virtual reality; A, natural decorative paintings; B, indoor potted plants; C, ornamental fish.

As for the short-term VR intervention trial, a total of 64 participants over 60 years old with diabetes are recruited. The participants are randomly assigned to seven intervention groups or a control group using block randomization with randomly selected block sizes. The main objective of the short-term trial is to determine which biophilic elements or their combinations show the most significant improvement in cognitive function.

As for the long-term real environment intervention trial, a total of 240 participants over 60 years old with diabetes will be recruited. The participants will be randomly assigned in a 1:1 ratio to either the intervention or control group. The main objectives of this long-term trial are to provide evidence for the healing effects of biophilic environments on cognition, and whether the *APOE4* genotype will modify the healing effects of biophilic environments on cognition in elderly diabetes.

Enrollment completion and final study visit are projected for December 2024 and December 2026, respectively.

This study was approved by the Ethics Committee of Capital Medical University (Approval No: Z2023SY019) and is conducted according to the ethical standards of the Helsinki Declaration. The study protocol was developed according to the Standard Protocol Items: Recommendations for Interventional Trials (SPIRIT) checklist.

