#### Long-term real environment intervention trial

2.11.2

The randomized block analysis of the variance module of PASS 11.0 was used to calculate the sample size. Due to the lack of long-term longitudinal studies on the impact of biophilic living environments on the MoCA scores in elderly diabetic patients, we referred to studies on the impact of natural environments on cognitive scores. Changes in cognitive scores ranged from 0.020 to 0.029 for each interquartile range shift in the Normalized Difference Vegetation Index (NDVI) (De Keijzer et al., 2018). Based on these findings, we set the between-group difference in cognitive scores at 0.02, with a standard deviation of 0.017, an intraclass correlation coefficient of 0.02, and the number of blocks was set at 2. With these parameters, achieving a statistical power of 90% at the 0.05 level of two-sided significant difference requires 99 participants per group. Accounting for about 20% loss to follow-up, each group will initially need to enroll at least 120 participants, totaling 240 participants across both intervention and control groups. Considering that our participants are older adults, the likelihood of noncompliance is higher than others. Therefore, we chose a 20% non-compliance rate to ensure the study has sufficient statistical power.

Furthermore, the logistic regression module of PASS11.0 was used to calculate the sample size required for analyzing the association between the *APOE4* genotype and cognitive function. According to previous research, the prevalence of MCI in Chinese people aged 60 years and older is about 15% (Jia et al., 2020), the odds ratio of the association between *APOE4* and cognitive impairment in the Chinese population was about 2.5 (Jiang et al., 2017), the *R*^2^ of *APOE4* with other covariates, such as age and gender, is about 0.05, with the significance level was set at 0.05. Based on these parameters, achieving a power of 90% in a two-sided test requires 103 participants. In summary, the long-term trial will include at least 120 subjects in each group.

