#### Long-term real environment intervention trial

2.12.2

The modified intention-to-treat population (mITT) will be used for statistical analysis. Missing values will be imputed using multiple imputation. Firstly, two sample t-tests (for continuous and normally distributed variables) and chi-square test (for categorical variables) will be conducted to assess the baseline equivalence between the intervention and control groups. Two sample t-tests will be used to compare whether cognitive scores are statistically different between two groups. Multiple linear regression will be used to demonstrate whether the intervention is statistically associated with cognitive scores after adjusting for potential confounders. Repeated measures ANOVA will be used to compare cognitive scores across groups. The potential confounders will be corrected in the mixed-effect model to determine the association between intervention and cognitive scores. If the intervention has a direct effect on cognitive function, longitudinal causal mediation analysis will be further used to clarify the mediating factors through which the intervention may affect cognition.

To explore the interaction of *APOE4* and the biophilic environment on cognition, we will perform stratified analysis according to groups to clarify the main effects of *APOE4* on cognitive function. Then, mixed models will be used to adjust for potential covariates and to elucidate the main effect of *APOE4* on cognitive function in each group. Finally, the interaction term between the *APOE4* and the intervention group will be included in the mixed-effects model to identify the effect of the genetic-environmental interaction on cognitive function.

In our study, all statistical tests are two-tailed, with a significance level of *p* < 0.05.

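### One 20% increase, from 99 to 120 per group, is labelled both loss to follow-up and non-compliance; on the plan's own 99 it falls short for loss and does not offset dilution

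*Protocol article*

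**What the plan says.** All of this is in section 2.11.2 (sample size, long-term trial) of the protocol article unless noted.

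- Base requirement: "achieving a statistical power of 90% at the 0.05 level of two-sided significant difference requires 99 participants per group".
- Inputs to it: "we set the between-group difference in cognitive scores at 0.02, with a standard deviation of 0.017". The same sentence adds "an intraclass correlation coefficient of 0.02, and the number of blocks was set at 2".
- The increase: "Accounting for about 20% loss to follow-up, each group will initially need to enroll at least 120 participants", which makes 240 in total.
- The paragraph then notes that older adults are more likely than others not to comply, and concludes: "Therefore, we chose a 20% non-compliance rate to ensure the study has sufficient statistical power".

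There is one increase in numbers and no reduction of the 0.02 difference. In section 2.12.2 the analysis set is given as follows: "The modified intention-to-treat population (mITT) will be used for statistical analysis". Missing values are to be multiply imputed. Nothing there says that participants who do not use the elements are left out.

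**The concern.** The paragraph gives one allowance two meanings and attaches a promise about power to it. The two meanings need different corrections. Loss to follow-up reduces the number of outcomes and can be made good by enrolling more people, by dividing by one minus the loss rate. A non-complier who is still analysed in the intervention group costs no outcome but pulls the group means together. That is corrected by shrinking the expected difference, and the required number then grows with the inverse square of the shrinkage. Multiplying the head count by 1.2 is the right correction for neither.

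The plan itself expects more non-compliance than in other populations. If the 24-month comparison shows no difference, readers will want to know whether dilution could explain it. They would be relying on a statement that the allowance had taken care of this, and the arithmetic in the same paragraph does not support that statement.

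**Working it through.** **Inputs.** From section 2.11.2: 99 per group, 90% power, two-sided 0.05, 120 enrolled per group, 20%, difference 0.02, standard deviation 0.017, intraclass correlation 0.02. Allocation is 1:1 (section 2.1).

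**Step 1: reproduce the plan's figures.**
- Base number: 2 × [0.017 × (1.960 + 1.2816)/0.02]² = 15.2, so 16 per group (17 with the noncentral t). Design effects of 1 + (m − 1) × 0.02, with m from 8 to 120, raise this to about 54 at most. No variant tried gave 99, so the 99 is not reproduced.
- Increase: 99 × 1.2 = 118.8, which rounds up to 120. This is a single 20% head-count increase.

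Steps 2 to 4 take 99 per group = 90% power as given. With n analysed per group and the difference multiplied by f,

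power = Φ(3.2415 × √(n/99) × f − 1.960).

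**Step 2: the 20% is loss.** 120 × 0.8 = 96, which is below 99. Power = Φ(3.2415 × 0.9847 − 1.960) = Φ(1.232) = 89.1%. The correct allowance is 99/0.8 = 123.75, so 124. With 120 enrolled, 99 remain only if loss is at most 1 − 99/120 = 17.5%.

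**Step 3: the 20% is non-compliance, and those people stay in the analysis.** If non-compliers keep a share k of the effect, f = 1 − 0.2 × (1 − k). With no loss, n = 120.
- k = 0: f = 0.8, power = Φ(3.2415 × 1.1010 × 0.8 − 1.960) = Φ(0.895) = 81.5%.
- k = 0.5: f = 0.9, power = Φ(1.252) = 89.5%.
- Break-even: 120 offsets the dilution when f ≥ √(99/120) = 0.908, that is when k is at least 1 − 0.092/0.2 = 0.54.
- With k = 0 the analysed number must rise by 1/0.8² = 1.56, to 99/0.64 = 154.7, so 155. The plan multiplies by 1.2.

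**Step 4: both, as two separate rates.** n = 96.
- k = 0: Φ(3.2415 × 0.9847 × 0.8 − 1.960) = Φ(0.594) = 72.4%.
- k = 0.5: 81.9%.
- Holding 90% with k = 0 would need 99/0.64/0.8 = 193.4, so 194 enrolled per group.

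| Meaning of the 20% | Analysed per group | f | Power if 99 = 90% |
|---|---|---|---|
| Loss only | 96 | 1.0 | 89.1% |
| Non-compliance only, half effect kept | 120 | 0.9 | 89.5% |
| Non-compliance only, no effect | 120 | 0.8 | 81.5% |
| Both, half effect kept | 96 | 0.9 | 81.9% |
| Both, no effect | 96 | 0.8 | 72.4% |

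The noncentral t at the same standardised difference (0.461) agrees within half a percentage point.

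**Step 5: the same stress on the printed inputs instead of the 99.** The diluted difference is 0.8 × 0.02 = 0.016. With standard deviation 0.017 this needs 24 analysed, or 30 enrolled, per group. Then 96 per group has over 99.9% power, and about 94% to 99.7% with design effects for m = 120 down to 48.

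**The case against.** The strongest reply is that the power figures hang on a number the plan cannot support. A reader might infer from them that 120 per group cannot hold 90% power. The documents do not establish this. On the stated difference and standard deviation, power stays at about 94% or higher even after 20% loss and full dilution (step 5). This stands: the percentages are conditional on the 99. It does not rescue the step itself. The plan presents 99 as its requirement, and the wrong form of correction would carry over to any other base number.

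A reader might also take 72% as the trial's power. That needs two separate 20% rates, and the text most naturally gives one, with the remark about older adults explaining why 20% was chosen. Section 2.11.1 likewise handles non-compliance or refusal by a 20% head-count increase, so the word may only mean failure to complete. This stands too. In that case the loss calculation applies, and the shortfall is about one point.

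Other points carry some weight:
- The mITT set is not defined in the article, so keeping non-compliers in it is an assumption, though the usual one.
- Imputation and the 12-month DSST may recover some information from people missing at 24 months, so 96 is pessimistic for that outcome.
- Monthly contact and replacement of elements (section 2.14.2) may limit non-compliance, but the plan still chose 20%.
- The 0.02 is the bottom of the cited range of 0.020 to 0.029, and 0.025 × 0.8 = 0.02. The section does not say, however, that 0.02 already allows for dilution.

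**Conclusion.** The point holds in a limited form. One 20% increase carries two labels, and the claim that it ensures sufficient power does not follow from it. Conditional on 99 per group for 90% power:

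- as loss, it misses its own target by 3 per group (96 against 99; about 89% power), which is minor;
- as non-compliance in an analysis that keeps everyone, power is about 81% if non-compliers gain nothing and about 89% if they keep half the effect;
- about 72% is a worst case that needs a separate 20% loss, no benefit at all in non-compliers, and an mITT set that retains them.

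The calculation assumes that controls are not contaminated. It does not show that the trial is underpowered, because the 99 does not reproduce from the plan's own inputs. That is the more basic problem and has to be settled first. What can be said now is that the stated assurance is unsupported and the form of the adjustment is wrong.

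**What to change.** Keep 240 participants and rewrite the paragraph in section 2.11.2:

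1. Say whether the 20% is loss to follow-up, non-compliance or both, with a rate for each that applies.
2. For loss, divide the required number by (1 − loss rate); on the printed 99 this gives 124.
3. For non-compliance, multiply the expected difference by (1 − rate), or by a stated factor if partial benefit is assumed. If 0.02 is meant to include dilution already, say so and make no second adjustment.
4. Reproduce the base calculation, then state the power that 240 gives under these adjustments. Until then, quote 89%, 81% or 72% only as conditional on 99 per group.
5. Remove the claim that the 20% allowance ensures sufficient power.

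The cost is one rewritten paragraph and a rerun of the base calculation, with no added participants. On the 99 basis the stated power becomes less favourable.

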### Statistical analysis

2.12

#### Short-term VR intervention trial

2.12.1

The analysis will be carried out according to the intention-to-treat principle. Given the short duration of this trial, missing data is expected to be minimal. Therefore, a single imputation will be used to process the incomplete data. Outliers will be identified using the interquartile range (IQR) method, defined as values below Q1 − (1.5 × IQR) or above Q3 + (1.5 × IQR), and will be replaced with Q1 − (1.5 × IQR) and Q3 + (1.5 × IQR), respectively. One-way analysis of variance (ANOVA) (for continuous and normally distributed variables) and chi-square test (for categorical variables) will be conducted to assess the baseline equivalence between the eight groups. If there are differences in characteristics between groups at baseline, the differences will be adjusted by performing multiple linear regression. ANOVA will be used to compare whether there are statistically significant differences in cognitive scores, heart rate and blood pressure among the eight groups. For each group, paired *t*-tests will be conducted to examine whether changes in cognitive scores, heart rate, and blood pressure are statistically significant between baseline, pre-intervention, and post-intervention. The identification of optimal biophilic elements will follow a two-stage analytic protocol. First, multiple linear regression models adjusted for covariates will be fitted to compare post-VR intervention cognitive scores between each intervention group and the control. Groups achieving a covariate-adjusted *p* < 0.1 in these pairwise comparisons will be considered statistically promising. Subsequently, among these candidate groups, the intervention demonstrating the largest adjusted mean difference in cognitive scores relative to the control group will be selected for long-term real environment intervention. Multiple linear regression will be used to evaluate the cognitive improvement in each group after adjusting for covariates. Continuous variables will be assessed for normality prior to analysis. If the data are not normally distributed, the Kruskal-Wallis H test will be used to compare the differences between the eight groups.

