**Figure 2 fig2:**
[figure not shown]
Short-term trial flow chart. A, natural decorative paintings; B, indoor potted plants; C, ornamental fish; VR, virtual reality; DSST, the Digit Symbol Substitution Test; BDS, the Backward Digit Span; SD, the Environmental Semantics Differential Scale; RS, the Restoration Scale.

During the VR experience, researchers record participants’ motion sickness. If participants feel nauseous or dizzy, they are instructed to remove the VR headset and take a two-minute break. Those who recover resume the trial, whereas those who remain symptomatic are withdrawn from the study.

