#### Short-term VR intervention trial

2.9.1

The DSST and BDS tests have been widely used in the field of VR environments for cognitive function, and they are highly responsive to the immediate effects of short-term interventions (Liu et al., 2022; Yin et al., 2018). Therefore, cognitive function is assessed by DSST (score range: 0–90) and BDS (score range: 0–9) scales. The DSST test is a simple and fast assessment tool that measures the ability to link symbols with numbers in 90 s (Beres and Baron, 1981). The DSST score is the number of symbols correctly filled in consecutively within 90 s. In the BDS scale, testing begins with three-digit numbers, which are read aloud to the participant, who is then required to repeat them in reverse. The test progresses sequentially to nine-digit numbers, with each sequence allowing up to two attempts. If a participant fails to correctly repeat a sequence of a specified length twice consecutively, the test is stopped. The number of digits in the longest correctly repeated sequence serves as the measure of cognition.

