#### Short-term VR intervention trial

2.11.1

The randomized block analysis of the variance module of PASS 11.0 was used to calculate the sample size. According to previous literature (Liao et al., 2020), the MoCA scores would increase by 0.5 points, and the Chinese version of the Verbal Learning Test (CVVLT) immediate recall scores would increase by 1.0 point after VR intervention. The DSST has been found to be more sensitive than the MoCA and CVVLT. Thus, we conservatively assumed that the mean difference in DSST scores between the intervention and control groups would be 1.0, with a standard deviation of 1.2. The number of blocks was set at 8, the significance level was set at *p* < 0.05 and the statistical power was set at 90%. Based on the above parameters, the minimum sample size per block is six individuals. Considering the possibility of noncompliance or refusal to participate, the sample size was increased by 20%, resulting in eight individuals per block. Thus, there are eight blocks in the short-term trial, with each block containing eight individuals.

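### Short-term trial: single imputation and IQR-fence replacement apply to the primary DSST and BDS scores, and under choices the article leaves open they can push the p<0.1 screen above its nominal error

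*Protocol article*

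**What the plan says.** Section 2.12.1 (statistical analysis, short-term VR trial) sets two data rules after stating the intention-to-treat principle.

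- **Missing data.** Because the trial is short, "missing data is expected to be minimal". "Therefore, a single imputation will be used to process the incomplete data". The method of imputation is not named.
- **Outliers.** "Outliers will be identified using the interquartile range (IQR) method". Values outside Q1 − 1.5×IQR and Q3 + 1.5×IQR are set to those limits. The rule is not restricted to particular variables or time points. It does not say whether quartiles are taken over all 64 participants or within each group.

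The same section then uses the scores to choose the long-term intervention: "Groups achieving a covariate-adjusted *p* < 0.1 in these pairwise comparisons will be considered statistically promising". Among the groups that pass, the one with the largest adjusted difference from control goes forward. Section 2.12.2 closes with the statement that "all statistical tests are two-tailed, with a significance level of *p* < 0.05". The 0.1 screen is therefore read here as two-sided.

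Three other places bear on the point:

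- Section 2.11.1: "Considering the possibility of noncompliance or refusal to participate, the sample size was increased by 20" per cent, giving eight per group.
- Section 2.5.1: after a break for nausea or dizziness during VR, "those who remain symptomatic are withdrawn from the study". This happens before the post-VR test.
- Section 2.9.1, on the BDS: "The number of digits in the longest correctly repeated sequence serves as the measure of cognition". Testing starts at three digits and ends at nine.

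For the long-term trial, section 2.12.2 plans multiple imputation.

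**The concern.** The two rules act differently.

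Single imputation supplies a score where there is none, and the regression then treats it as a measurement. In a group of eight, one such score is 12.5% of the group. If the filled-in value comes from the group's own data, the group mean looks more precise than it is and p-values come out too small. Withdrawal for persisting VR symptoms is a stated route to missing post-VR scores, and it is tied to the exposure.

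Fence replacement changes scores that were recorded. Cognitive outcomes are collected by assessors blinded to group (section 2.7.1), data are double-entered (section 2.13), and range and logic checks are done on site (section 2.14). An extreme DSST or BDS score that survives these checks is most likely real performance. Replacing it on a statistical criterion alone discards information, and on the BDS it can create a score the test cannot give.

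At stake is the reliability of the screen that fixes the intervention for a trial of 240 people.

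**Working it through.** **Inputs from the article.** 8 groups of 8; 7 comparisons with control; two-sided p<0.1; DSST difference 1.0 with SD 1.2 (section 2.11.1).

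**Assumptions.** Missing rates of 5%, 10% and 20%, completely at random (no rate is given); baseline to post-VR correlation 0.7 in the adjusted model; normal scores unless stated. The BDS-like distribution puts probabilities 0.05, 0.25, 0.35, 0.22, 0.09, 0.03 and 0.01 on scores 0, 3, 4, 5, 6, 7 and 8.

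**1. Nominal figure.** With complete, unaltered normal data the simulated error per comparison is 0.099 to 0.102, which reproduces 0.10. Runs were 20,000 to 40,000 trials.

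**2. Single imputation in closed form (group mean).** With k of n = 8 imputed in each of G = 8 groups, the true variance of a group mean is σ²/(n−k). The model uses σ²/n and divides a residual sum of squares with G(n−k−1) real degrees of freedom by G(n−1). The ratio of reported to true standard error is

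r = √[ (n−k−1)/(n−1) × (n−k)/n ],

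and the real error is P(|t| on G(n−k−1) df > r × 1.6725), where 1.6725 is the 95th percentile of t on 56 df.

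- k = 1 (12.5% missing): r = √(6/7 × 7/8) = 0.866; cut-off 1.448 on 48 df; error **0.154**.
- k = 2 (25% missing): r = √(5/7 × 6/8) = 0.732; cut-off 1.224 on 40 df; error **0.228**.

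**3. Single imputation by simulation, covariate-adjusted model.**

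| Method | 5% | 10% | 20% |
|---|---|---|---|
| Group mean | 0.120 | 0.145 | 0.206 |
| Regression including group | 0.122 | 0.144 | 0.208 |
| Stochastic regression | 0.118 | 0.142 | 0.186 |
| Grand mean; baseline carried forward | 0.098–0.100 | 0.098–0.100 | 0.098–0.100 |

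In separate unadjusted two-group t-tests, the regression methods are milder: 0.123 and 0.121 at 10%, 0.151 and 0.141 at 20%. The planned screen is covariate-adjusted, so the table applies.

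**4. Fence rule alone, no missing data.**

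- Quartiles over all 64: error 0.098 to 0.102 for normal, t with 3 df, skewed and BDS-like data. Power for 1.0/1.2 at p<0.1 is 0.499 with fences and 0.502 without.
- Quartiles within groups of 8: 0.115–0.117 (normal), 0.120 (t with 3 df), 0.132 (BDS-like), 0.133–0.142 (skewed).
- Share of scores altered: pooled 1.2% (normal) and 2.6% (BDS-like); within group 4.1% and 8.1%.

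**5. BDS values.** The possible scores are 0 and 3 to 9. If Q1 = 3 and Q3 = 4, the IQR is 1 and the fences are 3 − 1.5 = 1.5 and 4 + 1.5 = 5.5. Every 6 to 9 becomes 5.5 and every 0 becomes 1.5, neither of which the test can produce. If Q1 = 3 and Q3 = 5, the fences are 0 and 8, and only a 9 changes. Neither pair of quartiles is in the article.

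**6. Both rules together** (regression imputation, within-group fences, normal data): 0.137, 0.168 and 0.230 per comparison at 5%, 10% and 20% missing. The chance that at least one of seven groups passes under the null is 0.50, 0.58 and 0.71, against 0.40 with neither rule.

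**7. After the fix.** Observed scores only, no fences: 0.098 to 0.101 at all three rates. Multiple imputation (20 sets, small-sample df, 3,000 trials): 0.098, 0.100 and 0.097.

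**The case against.** A reader might infer that the two rules, as written, make the screen too liberal. The article does not support that. Pooled fences leave the error at 0.10, and so do grand-mean imputation and baseline carried forward. The article fixes neither the method nor the scope, and may leave both to an analysis plan. This stands, and it makes the conclusion on error rates conditional.

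A reader might also set the 20% allowance against the expectation of little missing data. The allowance covers noncompliance and refusal. Someone who refuses need not generate a missing score, and a non-complier can still be tested. The trial is one short session. So 20% serves only as an assumed upper bound, and at 5% the inflation is small. Motion-sickness withdrawal is a real route to missing scores, but no rate is given.

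Nor does imputation overwrite recorded values; only the fence rule does that. The fences act on scores and not on changes, so they pull in high scorers, who are not necessarily the best responders.

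Finally, the screen only selects an element, which is then tested in a separately randomised trial, so a liberal screen does not inflate that trial's error. The seven uncorrected comparisons already give about a 0.40 chance of at least one false pass; that is a larger and separate matter.

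None of this supplies a reason to keep either rule. With pooled quartiles the fences bring no gain in power, and multiple imputation is already planned for the other trial.

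**Conclusion.** The point holds in conditional form. Section 2.12.1 applies single imputation and fence replacement to the primary scores without exemption, and those scores drive the choice of long-term intervention.

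- Imputation from the participant's own group takes the nominal 0.10 to about 0.12, 0.14 and 0.19–0.21 at 5%, 10% and 20% missing. Other single-imputation methods do not.
- Within-group fences take it to about 0.12–0.14. Pooled fences do not.
- Whatever the effect on error, the fence rule alters genuine scores and can yield impossible BDS values.

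These sizes rest on the assumed missing rates, data missing completely at random, a correlation of 0.7 and illustrative score distributions. Bias from symptom-related withdrawal was not quantified. The stated rules should be changed, but this is not a fatal flaw.

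**What to change.** In section 2.12.1:

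- Replace single imputation. In the covariate-adjusted screening model, analyse observed scores, or fit a likelihood-based model to the baseline, post-stress and post-VR scores, or use multiple imputation as section 2.12.2 already does.
- Remove fence replacement from the main analysis of DSST and BDS. Correct only verified data errors and analyse the scores as recorded.
- If fence replacement is kept, report it as a sensitivity analysis only, with quartiles computed over all participants without regard to treatment.

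The cost is analysis wording and a little programming; design, sample size and data collection do not change.

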### Randomization

2.10

Randomization is conducted by a computer-generated list of random numbers made by independent statisticians without any clinical involvement in the study. The block randomization sequence is generated using SAS 9.4 software (PROC PLAN). The randomized block sizes are set to 8 and 16 for the short-term VR intervention trial and 2 and 4 for the long-term real environment intervention trial. After obtaining eligible patient consent, allocations are determined using sequentially numbered sealed envelopes containing information disclosing the type of intervention to be applied. Additionally, group assignments will be concealed until the intervention begins.

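### The VR trial's 90% power comes from a randomised-block calculation that fits neither its randomisation nor its eight-arm analysis; with eight per arm each scene-versus-control comparison has about 37% power at 0.05 and 50% at p<0.1

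*Protocol article*

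**What the plan says.** **Sample size (2.11.1).** The method is given as "The randomized block analysis of the variance module of PASS 11.0 was used to calculate the sample size". The assumption is a "mean difference in DSST scores between the intervention and control groups would be 1.0, with a standard deviation of 1.2", at significance level 0.05 and 90% power. The block input is "The number of blocks was set at 8". The result is a minimum of six people per block, raised by 20% to eight, and the section ends: "Thus, there are eight blocks in the short-term trial, with each block containing eight individuals".

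**Design and Randomization (2.1, 2.10).** Section 2.1 says allocation is made "using block randomization with randomly selected block sizes". Section 2.10 adds: "The randomized block sizes are set to 8 and 16 for the short-term VR intervention trial".

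**Statistical analysis (2.12.1).** "ANOVA will be used to compare whether there are statistically significant differences in cognitive scores, heart rate and blood pressure among the eight groups". The element for the long-term trial is then chosen in two steps. Covariate-adjusted linear regressions compare each scene with control, and scenes with p<0.1 are kept. Among those, the scene with the largest adjusted mean difference is taken forward. The covariates are not listed, and no block factor is named.

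**The concern.** The three sections do not describe one design. Read literally, the block structure in 2.11.1 is only one special case of what 2.10 can produce, and a block of six could not hold one person from each of eight arms. The sizing model is also not the model that 2.12.1 describes, and it is run at 0.05 while the selection is made at p<0.1.

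This matters because the VR regressions decide which element goes into the 24-month, 240-person trial. A reader of 2.11.1 would believe that a scene with the assumed benefit has a 90% chance of being detected. If the calculation was made for a different layout, that chance may be far lower, and the scene taken forward is much less securely chosen than the text suggests.

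**Working it through.** **Inputs.** From 2.11.1: difference 1.0, SD 1.2, alpha 0.05, power 90%, 8 blocks, minimum six, inflated to eight. From 2.10: block sizes 8 and 16. From 2.12.1: eight arms, pairwise screen at p<0.1. Tests are two-sided (2.12.2). The SD of 1.2 is taken as the error SD of the fitted model.

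**1. Block structure.** With *a* blocks of 8 and *b* blocks of 16, 8a + 16b = 64 gives a + b = 8 − b for b = 0 to 4, so 4 to 8 blocks. Eight blocks of eight arise only if size 16 is never drawn. Eight arms × 8 people = 64, so *block* in 2.11.1 reads naturally as *arm*. Section 2.11.2 fits this reading: it enters two blocks for a two-arm trial.

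**2. Reproducing the stated six at 90% power.**

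| Layout (difference 1.0, SD 1.2, alpha 0.05) | Needed for 90% | Power at six |
|---|---|---|
| Two-group comparison, normal formula | 31 per group | 30% |
| Eight-arm one-way ANOVA, control at 0, seven scenes at +1 | 31 per arm | 20% |
| Same, with blocks | 32 per arm | 19% |
| Eight arms, four at 0 and four at 1 | 15 per arm | 43–44% |
| Eight arms, 1.0 taken as the SD of the arm means | 5 per arm | 98.5–98.7% |
| Two arms in 8 blocks | 8 per block (90.6%) | 80.4% |

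For the first row, n = 2 × (1.96 + 1.28)² × 1.2² / 1.0² ≈ 30.2, rounded up to 31. Six is not the 90% answer in any row. It meets a conventional target only for two arms in eight blocks, and then 80%. The inflation step is sound: 6 × 1.2 = 7.2 and 6 / 0.8 = 7.5 both round up to 8.

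**3. Power of the comparison that selects the element.** With eight per arm, the SE of a scene-versus-control difference is 1.2 × √(2/8) = 0.60, and the noncentrality is 1.0 / 0.60 = 1.67. The noncentral t with 8 × 7 = 56 pooled error degrees of freedom gives:

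- alpha 0.05: 37% (34% with the 14 degrees of freedom of two groups alone)
- alpha 0.10: 50% (48%)

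If the 20% allowance is used up and six per arm remain, these fall to 29% and 41% (pooled error). For 90% power at eight per arm, the SD would have to be roughly 1 / (0.5 × 3.24) = 0.62 at 0.05, or 1 / (0.5 × 2.93) = 0.68 at 0.10, a little over half the assumed 1.2.

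**4. What a block term would change.** Simulation used 40,000 trials per setting: eight arms of eight, total SD 1.2, blocks all of size 8 or a mix of 8 and 16. The plan gives no within-block correlation for the VR trial, so the range is an assumption. The only value in the document, 0.02, belongs to the long-term trial.

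| Correlation | Error rate at p<0.1, without / with block | Power at p<0.1, without / with block | Excess SE without block |
|---|---|---|---|
| 0 | 10.0–10.2% / 10.0–10.1% | 50% / 50% | 0% |
| 0.02 | 9.5–9.7% / 9.9–10.1% | 50% / 51% | 1% |
| 0.05 | 9.2% / 9.8–10.0% | 50–51% / 52% | 2.5% |
| 0.10 | 8.4–8.5% / 10.0–10.1% | 50–51% / 54% | 5% |
| 0.20 | 6.9–7.4% / 10.1–10.2% | 50–51% / 57% | 11% |

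**The case against.** The strongest reply is that 2.11.1 simply says *block* where it means *arm*. Sections 2.10 and 2.11.1 then describe no rival randomisation schemes, and six per block is not an impossible block. That reading is probably right, and it reduces the block conflict to wording. It does not rescue the calculation: six per arm is not the 90% answer for the eight-arm layouts tried, and eight per arm gives the pairwise powers above.

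A second reply is that covariate adjustment may reduce the error SD. It may, but 1.2 is the plan's own figure, and it would have to fall to about 0.6 to 0.7.

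A reader might infer something stronger: that leaving block out makes the standard errors wrong and undermines the p<0.1 screen. The document does not support this.

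- The selection covariates are unnamed, so block is unstated rather than excluded, and such detail may sit in the full protocol or SAP. The term one-way is attached only to the baseline ANOVA.
- These are permuted blocks for balance in a single centre, with no stratum named. Complete blocks contain every arm equally often, so block effects cancel from the arm differences. Only the error term is affected, and in the conservative direction.
- Substantial losses need correlations of 0.2 or more, for which the document offers no basis.

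A reader might also infer that random blocks of 8 and 16 often fail to total 64. A figure of about one third follows only from independent, equally likely, unconstrained draws, and 2.10 states none of these. Both sizes divide 64, and the statisticians may have constrained the list.

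**Conclusion.** The concern holds for the sample size. The 90% power in 2.11.1 does not describe the trial that 2.10 randomises and 2.12.1 analyses. On the plan's own difference and SD, with all 64 people complete, each scene-versus-control comparison has about 37% power at 0.05 and about 50% at p<0.1. A scene with exactly the assumed benefit is therefore about as likely to miss the screen as to pass it. This rests on 1.2 being the error SD. The sizing software's actual inputs beyond those printed are not known.

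The absent block term is minor. It is negligible at a correlation of 0.02. At 0.1 it means an error rate of about 8% instead of 10% and about 3 points of power. It neither biases the selection nor explains the gap between 90% and 50%.

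**What to change.** 1. **Section 2.11.1.** Replace *block* by *arm* where arm is meant: eight arms of eight, 64 in all, randomised in permuted blocks of 8 or 16 as in 2.10. Withdraw the 90% figure and state the power for the planned analysis: about 50% per scene-versus-control comparison at two-sided p<0.1 (about 37% at 0.05) for a difference of 1.0 and SD 1.2. If a smaller residual SD is expected after covariate adjustment, give it with its source.
2. **Section 2.10.** Make the block wording agree with 2.11.1, and say that the list is built to total 64.
3. **Section 2.12.1 (minor).** Say whether the randomisation block is a model term. Preferably include it, as a random effect, in the eight-arm ANOVA and in the selection regressions.

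Cost: items 1 and 2 are wording and one recalculation, with no extra participants or visits. Item 3 uses data already held. Even as a fixed effect, block takes at most 7 of the 56 error degrees of freedom, and in the simulation (complete data, no other covariates) power stayed at 50% when blocks explained nothing.
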